
### Safety analysis

Based on the SAS dataset, Cox proportional risk model will be used to calculate and compare the hazard ratios (HR values) between the two groups for most of the safety endpoints. Poisson regression or negative binomial regression will be used to better fit the rare events. Adverse events and serious adverse events will be listed separately and analyzed in summary. In each treatment group, the number and percentage of adverse events will be summarized by tissue and organ category. All deaths and serious adverse events will be described in detail using case narrative style.

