## Methods/design

### Study design and setting

This is a multicenter, randomized, double-blinded, placebo-controlled study. Upon obtaining Institutional Review Board (IRB)- Ethics Committee’s approval (from each corresponding included center), recruitment of patients will begin. The study is scheduled to start on May 1, 2021, with a completion date on December 31, 2022. Patients will undergo a 1:1 double-blinded randomization to receive a one-year course of alendronate sodium vitamin D_3_ tablets (Gubangjia, The CSPC Ouyi Pharmaceutical Co., Ltd. Shijiazhuang, China) or placebo. The use of Tylenol for pain control will be permitted during the trial; however, it will be monitored and reported for future analysis. In addition, Vitamin D and calcium supplementation will be allowed for usage by study participants. The use of unmarketed drugs or other investigational drugs will be prohibited during the study period; otherwise, such patients will be excluded. Other bisphosphonates (such as zoledronic acid, risedronic acid, etc.) will be prohibited during the study period. Non-steroidal anti-inflammatory drugs and other topical drugs with analgesic effects will be prohibited during the study period. This study will be carried out in three domestic hospitals (Peking Union Medical College Hospital, Zhongshan Hospital of Fudan University, and The Third Affiliated Hospital of Southern Medical University) with a follow-up period of 2 years.

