### Sample size calculation

Based on a previous observation, the mean annual loss of the medial tibial cartilage volumes in knee OA patients is 4.5% [25]. The monthly intake of vitamin D (50,000 IU) would result in a serum vitamin D3 level > 60 nmol/L [26], and this, in turn, has been reported to correlate with a 2.2% annual absolute reduction in cartilage loss [27]. This can be translated into a risk reduction of 22% for knee replacement over a period of 2 years [28]. Our sample size calculation was conducted based on Cohen’s formula [29]. With a power level of 80% and alpha level of 0.05, 60 participants (30 in each group) were required to detect a 2.2% between-group difference in terms of medial tibial cartilage loss (WORMS scale) during the second assessment time-point (12 months). Losses to follow-up were not considered in our initial sample size calculation (*NCT04739592*); however, given the fact that both interventions will be administered for a year and patients will be followed up for 2 years after enrollment, we anticipate that around 10% will be lost to follow-up each year, so we increased our final sample size to 220 participants (110 in each group).

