### Statistical analysis

Retrieved data from each patient in both groups will be recorded at baseline and at each follow-up assessment period using Excel, which will then be entered into a software for analysis after the final assessment point has been met. All statistical analysis will be conducted by a third-party (not involved with our research in any way) using the Statistical Analysis System (SAS) Software for Windows (version 9.4, *SAS institute, USA*).

Baseline demographic and clinical variables will be presented in the form of number and percentages for categorical variables, while continuous variables will be presented as means and standard deviations (SD) or median and range if the data were normal or skewed, respectively.

Our primary outcome will be analyzed with the intention-to-treat (ITT) analysis and reported as the mean difference (MD) and corresponding 95% confidence interval (CI) in cartilage-WORMS score between the intervention and control groups using Student’s t-test. Secondary outcomes will then be analyzed at the final assessment. Pain will be analyzed as a categorical outcome using the chi-square test, while the differences in continuous determinants of pain (baseline variables) will analyzed using MANOVA test. The QoL will be analyzed and reported as the mean difference and its corresponding 95% CI between both interventions using t-test. Bone density and osteoporosis severity (measured by the Kellgren-Lawrence scale) will be analyzed as categorical outcomes (normal, low density, osteoporosis) using the Chi-square test. Meanwhile, differences in serum levels of inflammatory biomarkers between both groups will be measured using t-test. In order to account for missing data, survival analyses will be conducted while implementing the “last-observation carried forward” approach. Such data will be presented in Kaplan–Meier curves, showing the numbers of patients analyzed at each assessment timepoint. A *p*-value of less than 0.05 will indicate statistical significance.

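### Poisson or negative binomial regression is named as the method for rare safety events, but neither gives a finite rate ratio when one arm has no events (minor)

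*Protocol article*

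**What the plan says.** The Safety analysis section of the protocol article sets out two tiers of models. The bulk of the endpoints go to Cox regression: "Cox proportional risk model will be used to calculate and compare the hazard ratios (HR values) between the two groups for most of the safety" (the quote stops just short of the end of its sentence). The remainder are dealt with as follows: "Poisson regression or negative binomial regression will be used to better fit the rare events". The section names no test statistic, no exact or penalised method, and no rule for an arm without events.

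It also plans a descriptive layer. Adverse events and serious adverse events are listed separately. There is a summary by organ class: "In each treatment group, the number and percentage of adverse events will be summarized by tissue and organ category". And "All deaths and serious adverse events will be described in detail using case narrative style".

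Three other statements bear on the point. The Sample size calculation section settles on 110 patients per arm, after an initial 30 per arm. Allocation is 1:1 (Study design and setting). The Statistical analysis section says that a p-"value of less than 0.05 will indicate statistical significance", with SAS 9.4 as the software.

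**The concern.** The article does make a choice here: it moves rare events from Cox to Poisson or negative binomial regression on the ground that these fit rarity better. That ground does not hold. Negative binomial regression adds a dispersion parameter for over-dispersed counts, which a handful of events cannot estimate well. Poisson regression has the same weakness as Cox: with no events in one arm, the likelihood keeps rising as the log ratio grows, so there is no finite estimate.

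The stake is how rare harms are reported. A trial of this size is likely to see some events in one arm only. If the regression output is then read through its Wald test, the report shows an enormous ratio, an unbounded interval and a p-value near 1, whatever the size of the imbalance. If the test is chosen after the empty arm has been seen, the same data can yield very different p-values.

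**Working it through.** The article gives no safety rate, event count or power statement, so there is no figure of its own to reproduce. All event risks below are assumptions.

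**Inputs.** n = 110 per arm (Sample size calculation); 1:1 allocation (Study design and setting); threshold 0.05, taken as two-sided because the article does not say (Statistical analysis).

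**Step 1: how often is an arm empty?** With true risk p in both arms, one given arm has no events with probability q = (1 − p)^110. Exactly one arm is empty with probability 2q(1 − q); both are empty with probability q².

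| Assumed risk p | q | exactly one arm empty | both arms empty |
|---|---|---|---|
| 0.5% | 0.576 | 2 × 0.576 × 0.424 = 49% | 33% |
| 1% | 0.331 | 2 × 0.331 × 0.669 = 44% | 11% |
| 2% | 0.108 | 2 × 0.108 × 0.892 = 19% | 1% |

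The column that matters is exactly one arm empty. When both are empty, no method can say anything about the difference.

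**Step 2: what do the named models return for k versus 0 events?** Take k = 6 among 110 versus 0 among 110, at most one event per patient and equal follow-up.

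- Poisson, maximum likelihood: log rate ratio 22.4 with SE about 18,000 (the point at which the iteration stopped, not an estimate). Wald p = 0.999.
- Negative binomial with dispersion fixed at 1: Wald p = 0.999.
- Cox, with six illustrative event times within 12 months: Wald p = 0.9999; log-rank p = 0.013.

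For every k tried from 3 to 10, the Poisson and negative binomial Wald p-values stay at about 0.999.

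**Step 3: other analyses of the same 6 versus 0.**

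- Poisson likelihood-ratio test: χ² = 2k ln 2 = 2 × 6 × 0.693 = 8.32, p = 0.004.
- Poisson score test: χ² = k = 6, p = 0.014.
- Exact conditional Poisson test: p = 2 × 0.5⁶ = 0.031. The lower 95% limit of the rate ratio comes from π = 0.025^(1/6) = 0.541, giving 0.541/0.459 = 1.18; the upper limit is infinite.
- Fisher's exact test: p = 0.029.
- Risk difference: 6/110 − 0 = 5.5%, Newcombe 95% CI 1.0% to 11.4%.

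**Step 4: when would the verdict change?** Fisher's test gives 0.060 for 5 versus 0, 0.029 for 6 versus 0 and 0.0068 for 8 versus 0, so an exact test falls below 0.05 only from 6 versus 0 upward. The probability of no control events together with at least 6 treated events is 0.16 at assumed risks of 1% versus 5%, and 0.27 at 0.5% versus 5%.

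**The case against.** The strongest reply is that the failure is one of the Wald test and not of the model, and that the article does not ask for Wald tests. This is correct. The same Poisson fit supports a likelihood-ratio p of 0.004 and a score p of 0.014. A reader might infer that following the sentence as written forces a p-value near 1, or leaves nothing usable; the document does not support that.

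A reader might also infer that a real harm would be hidden and the safety conclusion wrong. That does not follow either. Counts and percentages per arm, separate listings and narratives for deaths and serious events are all planned, so 6 versus 0 would be plain to see.

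A third tempting reading is that percentages will be of events and not of patients, so that one patient with repeated events could dominate a category. The sentence can be read that way, but it may be no more than loose wording in a condensed article, and the denominator is normally fixed in the SAP.

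The probabilities in Step 1 also need care. They assume equal risk, so they show how often the estimate breaks down, not how often a true harm is missed. With fewer than six events against none, the exact test would not reach 0.05 either, and the gain is only an interpretable interval. Poisson regression is a conventional model for low rates and is finite when both arms have events.

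Finally, test statistics and handling of empty cells commonly belong in the SAP, which is not shown. That would dispose of a complaint about silence. It does not dispose of this point, because the article names a remedy for rarity and the remedy does not work in the situation that rarity most often produces.

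**Conclusion.** The point stands as a minor defect. The models assigned to rare events have no finite maximum-likelihood rate ratio when one arm is empty, and a Wald interval or p-value is then meaningless (0.999 for 6 versus 0, against 0.029 by Fisher's test). At 110 per arm, exactly one empty arm has probability 44% at an assumed common risk of 1% and 49% at 0.5%, falling to 19% at 2%. Cox fails in the same way, so moving rare events away from Cox does not help.

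The consequence is confined to the quality of the estimate and to an open choice of test, under which p for the same data runs from 0.004 to 0.999. It does not make the safety conclusion wrong. The size rests on assumed risks; the algebra of the empty arm does not, and the Wald result is the same at 30 per arm.

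**What to change.** Replace the sentence on rare events in the Safety analysis section along these lines:

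- For events seen in few patients (for example fewer than 10 in total) or in one arm only, report the number and percentage of patients with at least one event per arm, and the risk difference with a Newcombe or Miettinen-Nurminen 95% CI. If a ratio is wanted, give an exact conditional or Firth-penalised estimate.
- Keep Poisson or negative binomial regression for recurrent event counts, with follow-up time as offset.
- In the organ-class summary, state that percentages are of patients with at least one event, with event counts alongside.

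The cost is a few sentences of analysis wording. No new data are needed and the methods are available in SAS 9.4. The downside is that exact intervals are slightly conservative.

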### Sample size calculation

Based on a previous observation, the mean annual loss of the medial tibial cartilage volumes in knee OA patients is 4.5% [25]. The monthly intake of vitamin D (50,000 IU) would result in a serum vitamin D3 level > 60 nmol/L [26], and this, in turn, has been reported to correlate with a 2.2% annual absolute reduction in cartilage loss [27]. This can be translated into a risk reduction of 22% for knee replacement over a period of 2 years [28]. Our sample size calculation was conducted based on Cohen’s formula [29]. With a power level of 80% and alpha level of 0.05, 60 participants (30 in each group) were required to detect a 2.2% between-group difference in terms of medial tibial cartilage loss (WORMS scale) during the second assessment time-point (12 months). Losses to follow-up were not considered in our initial sample size calculation (*NCT04739592*); however, given the fact that both interventions will be administered for a year and patients will be followed up for 2 years after enrollment, we anticipate that around 10% will be lost to follow-up each year, so we increased our final sample size to 220 participants (110 in each group).

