**Methods:**

This multicenter, randomized, double-blinded, placebo-controlled study will evaluate the efficacy and safety of alendronate in early OA. Patients will undergo a 1:1 double-blinded randomization to receive a one-year course of either alendronate sodium vitamin D_3_ or placebo. The primary outcome is to compare WORMS score of knee joint at 6 and 12 months between both groups. Secondary endpoints will include WORMS score at 24 months, knee pain, radiographic progression of OA, severity of OA, quality of life, and serum inflammatory biomarkers at different assessment timepoints. To detect a 2.2% difference in cartilage loss between both groups with power of 80%, a sample size of 60 (30 per group) is proposed.

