### Outcome measures

#### Primary outcome

Our primary outcome is to determine the improvement in knee structure following each intervention using an MRI-based scale named the Whole-Organ Magnetic Resonance Imaging Score (WORMS) scale at 6 and 12 months after treatment allocation [20]. The WORMS scale is designed to determine the status of the knee joint in patients with OA in respect to fourteen independent articular features. Five out of the 14 features are related to the articular surfaces, and they include: (1) cartilage signal and morphology, (2) subarticular bone marrow abnormality, (3) subarticular cysts, (4) subarticular bone attrition, and (5) marginal osteophytes. In addition, all of these features are further evaluated in 15 different regions divided by anatomical landmarks in a fully-extended knee (Supplementary Fig. 1). For the purposes of our research, we will focus on cartilage signal and morphology. This feature is scored based on only 14 articular surface regions (excluding region S), with a score ranging from 0 to 6 on an 8-point scale (Supplementary Fig. 2). The WORMS scoring system for cartilage includes 0 = normal cartilage thickness and signal, 1 = normal cartilage thickness but with increased signal, 2 = a partial-thickness defect of < 1 cm in the greatest width, 2.5 = a full-thickness focal defect of < 1 cm in the greatest width, 3 = multiple regions having partial-thickness defects alternating with regions of normal thickness or defects > 1 cm, 4 = diffuse partial-thickness defects, 5 = multiple regions of full-thickness defects or defects > 1 cm, and 6 = diffuse full-thickness defects, with an overall score ranging from 0 to 84.

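### The 80% power is stated for a percent cartilage loss taken from vitamin D data, with no target difference or SD in WORMS points, so it is not established for the primary t-test on the 0–84 cartilage score

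*Protocol article*

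**What the plan says.** **Planning quantity** (Protocol article, Sample size calculation). The paragraph starts from a natural-history figure, given in percent: "the mean annual loss of the medial tibial cartilage volumes in knee OA patients is 4.5". It then argues that monthly vitamin D raises the serum level, which "has been reported to correlate with a 2.2% annual absolute reduction in cartilage loss". The size follows: "With a power level of 80% and alpha level of 0.05, 60 participants (30 in each group) were required". Its stated purpose, at the 12-month assessment, is to "detect a 2.2% between-group difference in terms of medial tibial cartilage loss (WORMS scale"). Only Cohen's formula is named. No SD and no standardised effect are given. The total is then raised to 220 (110 per group), with loss to follow-up of about 10% per year as the reason. The Abstract still gives 60.

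**Analysed quantity** (Primary outcome; Statistical analysis). The primary outcome is the WORMS cartilage signal and morphology feature: "This feature is scored based on only 14 articular surface regions (excluding region S), with a score ranging from 0 to 6 on an 8-point". The grades are summed to a total of 0 to 84. The result is reported as a between-group mean difference with a 95% CI, using Student's t-test. On the test level the section says only that a p-value "of less than 0.05 will indicate statistical significance".

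**Vitamin D and the object of the trial.** The active arm receives a tablet combining alendronate sodium and vitamin D3. Study design and setting adds that "Vitamin D and calcium supplementation will be allowed for usage by study participants", with no restriction by arm. The Abstract says that the trial "will evaluate the efficacy and safety of alendronate in early OA", while Trial objectives sets the combination against placebo.

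**The concern.** A power statement belongs to one test of one variable with one assumed spread. Here the effect size is a percentage of cartilage lost in one compartment, and the test is on a sum of ordinal grades across the knee. Adding the WORMS label in brackets after the percentage does not convert one into the other. A reader who takes the 80% at face value will believe that the primary comparison was sized for a known difference in the score, and the documents do not show this.

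What is at stake is how the result is read against the plan. Without a target in WORMS points, nobody can say which difference the trial was built to detect, or whether 220 patients are too few, enough, or more than needed.

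**Working it through.** **1. The two quantities side by side**

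| | Sample size calculation | Primary analysis |
|---|---|---|
| Variable | annual cartilage loss | cartilage-WORMS sum score |
| Unit | percent | points, 0–84 (14 regions × 6 = 84) |
| Region | medial tibia | 14 articular regions |
| Source of effect | vitamin D correlation | alendronate plus vitamin D3 versus placebo |
| Target difference | 2.2% | not stated |
| SD | not stated | not stated |

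**2. Can 60 be reproduced?** Not from the stated inputs, because there is no SD. It can only be solved backwards. Assumption: two-sided alpha 0.05, since sidedness is not stated.

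- Normal approximation: d = (1.960 + 0.842) × √(2/n). For n = 30 per arm, d = 2.802 × 0.258 = 0.72. With the noncentral t, d = 0.74.
- Implied SD on the percent-loss scale: 2.2 / 0.736 = 2.99, about 3.0 percentage points. The protocol does not state this value, and it says nothing about the SD of a 0–84 score.

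**3. What the final size fixes.** About 10% loss in the first year leaves 110 × 0.9 = 99 per arm at 12 months, which gives d = 0.40 for 80% power. The step to 220 supplies no effect size of its own: 60 / 0.8 = 75, so the stated dropout does not lead from 60 to 220.

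**4. Detectable difference in WORMS points at 80% power (d × SD, SDs assumed)**

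| SD (points) | 30 per arm | 99 per arm |
|---|---|---|
| 3 | 2.2 | 1.2 |
| 4 | 2.9 | 1.6 |
| 5 | 3.7 | 2.0 |
| 10 | 7.4 | 4.0 |

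**5. Power under one possible translation.** Assumption: 2.2% means 2.2% of the score range, 0.022 × 84 = 1.85 points. The documents do not say this. Power is the probability that a noncentral t with 2n − 2 degrees of freedom and noncentrality (1.85/SD) × √(n/2) exceeds the two-sided 5% limit.

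| SD (points) | d = 1.85/SD | 30 per arm | 99 per arm |
|---|---|---|---|
| 3 | 0.62 | 65% | 99% |
| 4 | 0.46 | 42% | 90% |
| 5 | 0.37 | 29% | 73% |
| 10 | 0.18 | 11% | 25% |

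The SD at which power is 80% is 1.85/0.736 = 2.5 points for 30 per arm and 1.85/0.400 = 4.6 points for 99 per arm.

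**6. Dilution by permitted vitamin D.** Assumption: a fraction f of placebo patients gains the planning benefit through supplements, so the difference becomes 2.2 × (1 − f), and the SD is the back-solved 2.99. For f = 0.3 the difference is 1.54 and d = 1.54/2.99 = 0.515. Power is 50% at 30 per arm, 95% at 99 and 97% at 110.

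**The case against.** **On power.** It can be said that the enrolled number is 220, not 60, and that this may well be ample. That stands as far as it goes: under the 1.85-point reading, 99 per arm gives 90% power or more if the SD is 4 or less. A reader might infer that the trial is underpowered. The documents do not support this, because that conclusion needs an SD of about 5 points or more and they favour no SD. For the same reason it cannot be said that a restated power would be less favourable. The larger number does not rescue the 80% claim either, since it is justified only as a dropout allowance and has no WORMS target of its own.

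**On dilution.** A reader might infer that vitamin D use in the placebo arm cuts power to about 50%. That holds only at 30 per arm with f = 0.3. At the planned size the same inputs leave about 95%. Nor do the supplement rule and the planning assumption strictly contradict each other: one permits a product, the other assumes an effect.

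**On vitamin D as the source.** The tested tablet contains vitamin D3, so the planning effect concerns one component of the product. This is a weak basis, but not an irrelevant one.

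**On attribution.** A reader might infer that the trial wrongly claims an effect of alendronate alone. Background, Trial objectives and the Abstract's Discussion already name the combination. What remains is shorthand in a few sentences.

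**On a null result.** It will be read from the 95% CI in WORMS points, which does not depend on the planned power. The defect biases neither the estimate nor the type I error.

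None of this touches the mismatch between the quantity that was powered and the quantity that is tested.

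**Conclusion.** The point holds for the mismatch of scale and the missing inputs. The 80% for 2.2% is stated for percent medial tibial cartilage loss, and the protocol gives nothing that carries it over to the t-test on the 0–84 score. All that the sample sizes fix is a standardised difference: 0.74 at 30 per arm and 0.40 at 99 per arm.

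The direction and size of any shortfall are unknown. Under the assumed 1.85-point target, power at 99 per arm runs from about 99% (SD 3) to about 25% (SD 10). These figures rest on a two-sided 5% level, 10% loss by 12 months, equal SDs and SD values chosen only for illustration.

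The vitamin D origin of the effect, the permitted supplements and the alendronate shorthand are minor notes.

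**What to change.** - Withdraw the statement of 80% power for a 2.2% difference, in Sample size calculation and in the Abstract.
- State the target as a between-arm difference in 12-month cartilage-WORMS points.
- Give an SD for the analysis actually planned. It can come from existing WORMS data or from the trial's pooled blinded data. If the analysis is to be baseline-adjusted, say so and state the assumed correlation between baseline and follow-up, because Statistical analysis currently specifies a plain t-test and a baseline SD alone is not enough.
- Keep 220 fixed and report the detectable difference over a range of SDs, as in step 4 of the working.
- Note that the planning effect concerns only the vitamin D component and could be diluted, because supplements are allowed in both arms.
- Align the alendronate-only shorthand in the Abstract, Trial objectives and Discussion with the combination-versus-placebo objective.

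The cost is a rewritten sample size paragraph, a search for a WORMS SD or a blinded look at pooled data, and small wording changes. No further patients need to be enrolled. The restated power may turn out better or worse than 80%.

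### Loss of about 10% a year turns 60 patients into 68 to 76, not 220; the abstract still proposes 60, and no power is stated for 220

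*Protocol article*

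**What the plan says.** The Sample size calculation section of the protocol article sets its error rates as follows: "With a power level of 80% and alpha level of 0.05". On that basis "60 participants (30 in each group) were required to detect a 2.2% between-group difference" at the 12-month assessment. The method is given only by name: "Our sample size calculation was conducted based on Cohen’s formula". The section adds that this initial figure left losses out of account.

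It then moves to a final figure in a single step. The reason is "we anticipate that around 10% will be lost to follow-up each year" over a two-year follow-up, and the conclusion is "so we increased our final sample size to 220 participants (110 in each group"). No other reason is offered, and no power is attached to 220.

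The Methods paragraph of the abstract gives the same 2.2% difference and 80% power, and ends with "a sample size of 60 (30 per group) is proposed". It does not mention 220.

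**The concern.** An allowance of 10% a year over one or two years is modest, but the step from 60 to 220 multiplies the trial by 220/60 = 3.7. The text presents the second number as a consequence of the first, so a reader can check it, and it does not follow.

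The enrolment target governs recruitment, the number of patients exposed to treatment or placebo, and how a null result is read. Here the article prints two targets, and the reason given does not connect them. If attrition is truly the only reason, 220 is 220 − 76 = 144 patients more than that reason supports, even at 24 months. If there is another reason for 220, it is not given, and neither is the power that the larger trial would have.

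**Working it through.** **Inputs from the document.** Sample size calculation section: alpha 0.05, power 80%, 60 participants (30 per group) without loss, a 2.2% difference at 12 months, about 10% loss per year, two years of follow-up, final size 220. Study design section: 1:1 allocation. Statistical analysis section: the primary result is "reported as the mean difference (MD) and corresponding 95% confidence interval (CI) in cartilage-WORMS score" "between the intervention and control groups using Student’s t-test".

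**Not in the document.** The SD (or standardised effect) and the sidedness of the test. The 95% CI points to a two-sided test; one-sided results are shown as well.

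**Step 1: try to reproduce 220.** The usual adjustment is N / (1 − loss), applied per arm and rounded up for equal arms.

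| Loss | Total | Per arm | Equal-arm total |
|---|---|---|---|
| 10% (12 months) | 60/0.90 = 66.7, so 67 | 30/0.90 = 33.3, so 34 | 68 |
| 19% (24 months, compounded) | 60/0.81 = 74.1, so 75 | 30/0.81 = 37.04, so 38 | 76 |
| 20% (24 months, added) | 60/0.80 = 75 | 30/0.80 = 37.5, so 38 | 76 |

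The cruder N × (1 + loss) gives 66 at 10% and 72 at 19% or 20%. No variant comes near 220. Working backwards, 220 would leave 60 evaluable only if the loss were 1 − 60/220 = 72.7%.

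**Step 2: the effect implied by 60.** Without an SD, the 60 cannot be recomputed. It can only be inverted, on the assumption that 30 per arm is an exact solution for 80% power.

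- Normal formula, two-sided: d = (1.960 + 0.842) × √(2/30) = 0.723, so SD = 2.2/0.723 = 3.04 points.
- Exact t-test, two-sided: d = 0.736, SD = 2.2/0.736 = 2.99 points.
- Exact t-test, one-sided: d = 0.650, SD = 2.2/0.650 = 3.39 points.

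**Step 3: power at each enrolment target under that effect.** Evaluable patients per arm are 30 × 0.90 = 27 and 30 × 0.81 = 24.3 for the smaller target, and 110 × 0.90 = 99 and 110 × 0.81 = 89.1 for the larger. Exact t-test results:

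| Enrolled | Evaluable per arm | Two-sided | One-sided |
|---|---|---|---|
| 60, no loss | 30 | 80.0% | 80.0% |
| 60, at 12 months | 27 | 75.6% | 76.1% |
| 60, at 24 months | 24.3 | 70.9% | 72.1% |
| 220, at 12 months | 99 | 99.9% | 99.8% |
| 220, at 24 months | 89.1 | 99.8% | 99.6% |

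The first row is 80% by construction. The 24-month rows show only what the same effect would give with fewer patients; the plan's calculation is for 12 months.

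**The case against.** The section does label its figures: the calculation without losses is the initial one and 220 is the final size. A careful reader can infer that 220 is the operative target and that the abstract was not updated. That stands, and it makes it speculative to suppose that the trial would be run to 60. It does not repair the reason given for 220, or the abstract.

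Enrolling more than the minimum is not an error in itself, and the SD may be in the full protocol that the article condenses. Both points stand. The missing SD alone is therefore not the complaint.

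A per-centre reading comes close: three hospitals × 60 = 180, and 180/0.81 = 222. But the section states 60 as the number needed for the comparison, not per hospital, and nothing in the article describes such reasoning.

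Three stronger readings are tempting, and the document does not support them:

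- *The 80% power belongs to neither size.* Both the abstract and the sample size section attach 80% to 60, and the section says that this is before loss. Nobody claims 80% for 220.
- *If 220 is right, 60 must have been derived wrongly.* For 99 per arm to give just 80% power for 2.2%, the SD would have to be about 5.5 points, and 30 per arm would then have only about 33% power. This presumes that 220 was itself sized for 80% power after loss, which the article does not say. Without an SD, the 60 can be neither confirmed nor refuted.
- *The target difference is unknown.* It is stated as 2.2% in both places. What is missing is a valid reason for 220 and its power.

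**Conclusion.** The point holds. As written, the stated loss does not lead from 60 to 220: it leads to 67 or 68 for the 12-month comparison and 75 or 76 for 24 months, and 220 would need about 73% loss. This part rests on no assumption beyond the document's own figures. The abstract contradicts the section on the enrolment target, and no power is given for the larger figure.

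The effect on power is conditional. It assumes that 60 is an exact t-test solution at alpha 0.05, so that d is about 0.74 and the SD about 3.0 points if two-sided, or d about 0.65 if one-sided. On that footing, 60 enrolled falls modestly short at 12 months, at about 76%, while 220 enrolled gives about 99.8 to 99.9%. A different SD would change these values. It would not change the failed step from 60 to 220.

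**What to change.** State one enrolment target, the same in the abstract and in the sample size section.

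- **If 220 stands:** delete the statement that attrition explains it and give its actual basis. Restate the power for the 2.2% difference with about 198 evaluable at 12 months (220 × 0.90) and about 178 at 24 months (220 × 0.81). Show the SD and the sidedness used.
- **If 60 evaluable patients are the requirement:** give the loss-adjusted target with equal arms, 68 if the allowance is for 12 months or 76 if it is for 24 months, and say which time point it protects.

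The cost is wording in two places and one recalculation by the trial statistician. Neither option needs patients beyond the 220 already stated. Whether the registry entry should change too cannot be judged from the article.
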